#### Exclusion criteria:

- Elective revision orthopedic surgery due to orthopedic infection within the last 12 months in the same area of surgery
- Emergency surgery (defined as planned surgery within the next 48 hours)
- Surgery on infected skin; or surgery under antibiotic treatment for any reason
- "Diabetic foot surgery" (distinct clinical entity; defined as below the ankle)
- Body mass index  $\geq 35$  kg/m^2 (anticipated difficulty of effective decolonization)
- Pregnancy (formality reasons)
- Intolerance or allergy to octenidin and/or ingredients in the octenisan® set
- Use of any other topical antiseptic agents other than octenisan® set (except for the duration of one day)
- Patient unable to understand; or under legal guardian for medical decisions
- Anticipated clinical follow-up of less than 6 weeks after surgery.
- ASA-Scores 1-2, and ASA-Score 5 (high risk of postoperative complications)
- Known skin colonization with antibiotic-multiresistant Gram-negative organisms defined by infection control protocols of Switzerland.

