### 7.2 Recruitment, screening and patient's instructions

The concerning patients will be screened every day by the clinicians and the study investigators during the presurgical surgical and anesthesiologic consultations. In case all inclusion and no exclusion criteria are met, the patient will be informed about the study by one of the investigators (see chapter 2.7) and orally instructed about the handling of the decolonization set. It is important that the study investigator instructs the patient (and his/her accompanying family members) directly. An instruction of the set handling by the surgeons or anesthesiologists alone will not be accepted.

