#### 8.1.1 Intervention treatment

The duration of pre-surgical decolonization is planned to be five days. However, when this pre-surgical time period is too short, the decolonization may also start at least 3 days before surgery and may be continued up to 2 days post-surgery. In case of post-surgery application, the patient will be washed with water and octenisan® wash lotion by their treating nurses. The patient will also return the empty/used set and answer to a short questionnaire during their hospital stay. The study team will recuperate the questionnaire during hospitalization.

During decolonization, patients are asked to change the bed linen and underwear every day and not to share towels, clothes and other textiles with their family or pets. They may use their habitual perfumes, but must not use other antiseptic agents, body lotions or moisturizer during the decolonization period.

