##### 9.1.3.2 Laboratory parameters

n/a. No study specific laboratory parameters will be assessed

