#### **9.1.4 Assessments in participants who prematurely stop the study**

Participants who prematurely stop the investigation are defined as patients who withdraw consent or who, in the opinion of the investigator, are no longer eligible to participate in the study. Where possible, such patients will complete an early-termination visit to undergo all assessments applicable to the corresponding (or next) scheduled study visit. For these patients, we will record eventual adverse events, physical examination, laboratory parameters, vital signs during a follow-up period determined by clinical control, which is usually up to one-year post intervention.

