##### **9.2.1 Enrolment (Visit 1)**

Information collected during routine pre-surgical consultation and during orthopaedic surgery is not study specific. This data will be used as general demographic information and medical history within the study in case of an orthopaedic infection and study participation.

If a patient appears to be eligible the following study-related procedures are performed:

1. Patient information and obtaining written informed consent.
2. Assign a study identification number.
3. Record/complete medical history and demographics.
4. Review inclusion/exclusion criteria.
5. Randomize the patient and handing out of the decolonization set.

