#### 11.3.2 Final analyses

The intent-to-treat (ITT) population will consist of all randomized patients. Patients will be analysed according to treatment group assignment. Patient disposition and baseline characteristics will be based on the ITT population.

The per-protocol (PP) population will consist of all randomized patients who complete the study (or who are otherwise defined as a treatment failure) according to the clinical investigation plan and who have not deviated significantly from the protocol. All efficacy analyses will be repeated using the PP population. Any analysis involving microbiological assessments will exclude patients without an assigned baseline pathogen.

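### Sections 9.1.4 and 9.2.5 let an unblinded investigator stop randomised patients for lost eligibility, and with 11.4 this can take them out of the ITT comparison

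*Protocol*

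**What the plan says.** **Eligibility and timing.** Section 7.1 lists among the exclusions "Surgery on infected skin; or surgery under antibiotic treatment for any reason". The study schedule marks the criteria only at Screening and Visit 1, and 7.2 places screening "during the presurgical surgical and anesthesiologic consultations". At Visit 1, section 9.2.1 puts the review of the criteria directly before its last step, "Randomize the patient and handing out of the decolonization set". The operation comes later. Section 8.1.1 says "The duration of pre-surgical decolonization is planned to be five days", with a start at least three days beforehand when time is short.

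**Stopping.** Section 9.1.4 counts as premature stops the patients who withdraw consent and also those "who, in the opinion of the investigator, are no longer eligible to participate in the study". Where possible they have an early-termination visit with the assessments of the corresponding or next visit. After that, "we will record eventual adverse events, physical examination, laboratory parameters, vital signs during a follow-up period determined by clinical control", usually for up to a year. Section 9.2.5 says that patients in this position will be terminated early, and includes those who need antibiotics beyond the end-of-treatment visit.

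**Analysis.** Section 11.3.2 says "The intent-to-treat (ITT) population will consist of all randomized patients". Section 11.4 makes missing outcome data a drop-out and excludes major deviations from ITT as well as per-protocol.

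**Text that points the other way.** Section 8.4 has withdrawn participants continue surveillance under the protocol. Section 9.2.3 promises every effort to obtain the primary outcome for all subjects. Section 7.4 allows study treatment to be stopped without withdrawing the patient, so that follow-up data can still be collected.

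**The concern.** Randomisation protects the comparison only if patients stay in it whatever happens after allocation. Here a patient who was properly eligible at Visit 1 can come to meet an exclusion criterion before surgery. The investigator who then decides whether that patient is still eligible knows the arm, because the trial is unblinded and investigators tell patients their assignment (6.2.1).

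Two things are at stake. First, patients who reach surgery with infected skin or on antibiotics may well carry a higher risk of SSI, so removing them changes the risk mix of those left. Second, loss of eligibility need not be equal between arms. Intolerance to the set is itself an exclusion criterion in 7.1, and section 3.6 anticipates more irritation, intolerance and allergy in the decolonization arm. That criterion would typically come to light only in patients who use the set. If such patients leave the comparison, the arms are no longer those that randomisation formed.

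**Working it through.** **Step 1: can the criterion become true after randomisation?** Criteria review and randomisation are consecutive steps at Visit 1 (9.2.1). Surgery follows a planned five, or at least three, days of decolonization (8.1.1), and 7.1 excludes surgery planned within 48 hours. So days lie between allocation and operation in both arms. The criterion refers to the operation, and no passage limits it to the state at randomisation. The answer is yes.

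**Step 2: what is recorded after a stop?** For a stop before surgery the next visit is Visit 2. Its list in 9.2.2 covers concomitant medication and additional interventions, adaptation of antibiotics, and adverse events. It contains no reading of the wound outcome at 6 weeks or 1 year. The later list in 9.1.4 covers adverse events, examination, laboratory values and vital signs. It names neither SSI nor wound revision.

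**Step 3: what happens in the analysis?** Under 11.3.2 the patient belongs to ITT. Under 11.4 the patient is a drop-out if the outcome is missing. If surgery under antibiotics or on infected skin is classed as a major deviation, the patient is excluded from ITT even with an outcome. The two sections cannot both be followed.

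**Step 4: the plan's own sample size.** Inputs: 10% and 5% (11.1), 80% power (11.2), two-sided 0.05 (11.3), 1:1 allocation (6.2.1). With d = 0.05 and mean rate 0.075:

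- n0 = [1.960·√(2·0.075·0.925) + 0.842·√(0.10·0.90 + 0.05·0.95)]² / 0.05² ≈ 434.4, so 435 per arm
- With continuity correction: n = (n0/4)·[1 + √(1 + 4/(n0·d))]² ≈ 473.6, so 474 per arm

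The stated 474 is reproduced. Rounding up to 500 leaves 26/500 = 5.2% per arm for loss from all causes.

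Continuity-corrected power, using n_eff = n·(1 − 1/(n·d))², is 82.3% at 500 per arm. With an assumed non-selective loss of 5% (475 per arm) it is 80.1%, and with 10% (450) it is 77.8%.

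**Step 5: illustration of bias.** The documents give no rate of later ineligibility and no risk for these patients, so every input here is an assumption except the 10% baseline. Suppose there is no true effect, risk is 10% in both arms, a share e is removed, and the removed patients have risk r. The analysed rate is (0.10 − r·e)/(1 − e).

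| Removed: control / decolonization | r | Analysed rates | Spurious difference in favour of decolonization |
|---|---|---|---|
| 2% / 5% | 20% | 9.80% / 9.47% | 0.3 points |
| 2% / 5% | 30% | 9.59% / 8.95% | 0.6 points |
| 5% / 10% | 20% | 9.47% / 8.89% | 0.6 points |
| 5% / 10% | 30% | 8.95% / 7.78% | 1.2 points |

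Swapping the shares reverses the sign. Equal shares with equal r give no bias but still lose outcomes: 3% of 1,000 episodes is 30.

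**The case against.** The strongest reply is that the protocol already places eligibility before randomisation and already intends full follow-up. The schedule has no later check of the criteria. Neighbouring exclusions describe a planned operation, and this one can be read the same way. Sections 7.4, 8.4 and 9.2.3 all favour continued follow-up. Section 9.1.4 keeps examination and adverse events, and 9.1 assesses the primary outcome visually. Section 10.1 collects serious adverse events to 42±14 days, or 1 year with an implant, and a revision that needs admission would be one of them.

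Much of this stands, and it rules out several stronger readings:

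- A reader might infer that the primary outcome of these patients is never collected. The documents do not say so. They contradict themselves, and some outcomes could be captured through examination or safety reporting.
- A reader might infer that 9.1.4 lists measurements the trial does not make, since 9.1.3.2 says "No study specific laboratory parameters will be assessed". That sentence and 9.1.3.3 rule out only study-specific measurements. Routine values may still be recorded.
- A reader might take the 30-day window in the schedule as the gap from randomisation to surgery. It labels the screening period; the documents do not state that gap.
- No passage orders the criteria to be applied again on the day of surgery. The stop depends on the investigator's judgement and is not automatic.

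The reply does not remove the problem. Sections 9.1.4 and 9.2.5 are the specific rules for patients judged ineligible after allocation, 9.2.5 says they will be terminated early, and nothing in 8.4 or 9.2.3 overrides 11.4. Staff cannot follow both sets of passages.

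**Conclusion.** The point holds as a contradiction with a real consequence. Followed as written, 9.1.4, 9.2.5 and 11.4 allow a discretionary exclusion after randomisation, by someone who knows the arm, against the ITT definition in 11.3.2 and the follow-up intended in 8.4 and 9.2.3. The sample size itself is not in error.

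The size is unknown. The 0.3 to 1.2 points above equal 6% to 24% of the 5-point target, but they rest wholly on assumed removal shares and risks, and they reverse or vanish as those change. They show what the rule permits, not a bias that can be expected. That the antiseptic alters skin infection or antibiotic use before surgery is conjecture. The documents support only the expectation of more intolerance reactions in the decolonization arm. Frequency may be small. The change is still worthwhile because it closes a selection route at almost no cost.

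**What to change.** - **7.1:** state that eligibility for the trial and its analysis is settled at the review immediately before randomisation.
- **9.1.4 and 9.2.5:** delete loss of eligibility as a ground for ending follow-up, in both places. Changing only one would leave the other in force.
- **9.1.4:** name SSI and unplanned wound revision, read at 6 weeks (or 1 year with an implant), as recorded for every randomised episode unless consent to data use is withdrawn. State that an assessment brought forward to an early stop does not replace that reading.
- **11.4:** let later ineligibility or a major deviation affect only the per-protocol population and never ITT, in line with 11.3.2.

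The cost is protocol wording, since section 9.2.3 says the study visits are part of routine care. The downside is that a few patients outside the intended population stay in ITT and slightly dilute the effect. How these patients are managed clinically is not addressed here; the protocol's own passages on that must be reconciled.

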The duration of pre-surgical decolonization is planned to be five days. However, when this pre-surgical time period is too short, the decolonization may also start at least 3 days before surgery and be continued up to 2 days post-surgery. During the post-surgery application, the patient will be washed with water and octenisan® by their treating nurses. The patient will also return the empty/used set and answer to a short questionnaire during their hospital stay. The study team will recuperate the questionnaire during hospitalization. We renounce on routine microbiological assessments of skin colonization, but the hospital's infection control can demand it for other reasons regarding infection control. Hence, skin colonization data will only be available for some selected patients that are screened for body carriage of antibiotic-resistant pathogens, according to the infection control recommendations in Switzerland.

There will be a Monitoring at study start, the interim analysis and at the end.

The primary study outcomes are unplanned revision surgery for SSI and wound problems at 42 days for all surgeries; or 1 year in case of an implant-related surgery. Secondary objectives are other unplanned revision surgeries for non-SSI reasons, all adverse events, as well as patient's subjective impression of the decolonization.

The treatment period includes the following daily study visits:

- Visit 1 - Enrollment (Day 1)
- End-of-Treatment (EOT) -Visit is the Day of Surgery or Day 1-2 after surgery
- Test-of-Cure-Visit (TOC) (clinical surgical control) - Day 42 (+/- 14 days)
- Further follow-up (eventually by phone call) for implant-related surgery - 1 year (+/- 2 months)

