#### 3.2.1 Study definitions

An orthopedic infection for this trial is the microbiological evidence of bacteria in at least two intraoperative tissue samples together with radiological (osteomyelitis, collections, inflammation) and/or clinical evidence of infection (pus, discharge, sinus tracts, rubor, calor, pain). Histological proof is facultative for this study. Implants are defined as any implants except for transient wires or fixator pins. A wound problem is any unplanned post-surgical wound pathology leading to surgical revision. Remission of infection is the absence of clinical and/or radiological and/or laboratory signs of (former) infection after the minimal follow-up time of 1 year for implant -related surgery with implants left in place; or two months for implant-free surgery (including surgery when all implants have been removed)..

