## 5. STUDY OUTCOMES

### Primary outcomes:

- Remission (and inversely superficial or deep-space SSI and revision surgeries for non-infected wound problems; composite primary outcome) at 6 weeks (and/or a 1 year for surgeries with implant)

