#### **9.2 Procedures at each visit for both prospective-randomized studies**

At enrollment (Visit 1 / Day 1), patients will be randomized at ratio 1:1 into the investigational group (decolonization) and the control group (no decolonization). The study investigators will instruct the correct decolonization procedure. During the decolonization period, patients can also review the patient information leaflet of the set for details on the decolonization procedure. The questionnaire will be handed over to the decolonization patients.

The treatment period includes the following study visits:

- Visit 1 - Enrollment (Day 1)
- Visit 2 - End-of-Treatment (EOT) -Visit is the Day of Surgery or Day 1-2 after surgery
- Visit 3 - Test-of-Cure-Visit (TOC) (clinical surgical control) - Day 42 (+/- 14 days)
- Follow-up (eventually by phone call) for implant-related surgery after 1 year (+/- 2 months).

During the study visits, we assess the history, wounds, adverse events, and the functional status. We examine the patients according to the orthopedic standard, and add supplementary laboratory exams and radiology, only if clinically indicated.

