##### **9.2.3 Visit 3 (Test-of-Cure)**

Every effort will be made to ensure that final efficacy assessments (i.e., primary outcome data) are available for all subjects. As all our study visits are part of the routine surgical and postsurgical assessments, we do not expect major drop-out rates; or drop out in very exceptional situations (e.g. transfer to another service because of stroke, non-infectious postsurgical fatalities, etc.) Outpatients should return to the clinic (assessments can be performed in the hospital for inpatients), where the following assessments will be performed:

1. Assess anamnestically all past adverse events of surgery, the hospitalization and decolonization
2. Record clinical and microbiological infection and its treatment (if any)

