### 11.4 Handling of missing data and drop-outs

Missing data regarding the outcome parameters and the decolonization will lead to patient dropout of the study. Drop-outs will be reported in the patients & methods section of the publication, drop-out of data will be reported for a minimum of 10 years after study termination or in case of premature termination of the clinical trial. Major deviations from the protocol will be regarded as drop-outs and excluded from both, the ITT and the PP populations. The independent Data Monitoring Committee may help in case of difficult interpretations of the case among the trial investigators.

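### The follow-up exclusion asks for 6 weeks from everyone, so an implant patient already expected to be unreachable at the 1-year primary time point is eligible

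*Protocol*

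**What the plan says.** **Availability.** The exclusion list in section 7.1, repeated in the synopsis, contains "Anticipated clinical follow-up of less than 6 weeks after surgery". It makes no distinction by implant. No other criterion concerns later availability.

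**Primary time point.** The synopsis (Study Conduct) gives the primary outcome as "unplanned revision surgery for SSI and wound problems at 42 days for all surgeries; or 1 year in case of an implant-related surgery". Section 5 words it more loosely: "at 6 weeks (and/or a 1 year for surgeries with implant", with remission as the outcome term.

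**Definition of remission.** Section 3.2.1 requires absence of signs of infection "after the minimal follow-up time of 1 year for implant -related surgery with implants left in place; or two months for implant-free surgery".

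**Contacts.** Section 9.2 schedules Visit 3 (Test-of-Cure) at day 42 +/- 14 days and then "Follow-up (eventually by phone call) for implant-related surgery after 1 year (+/- 2 months". Section 10.1 sets the study duration at 42 +/- 14 days, or 1 year with an implant.

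**Missing outcomes.** Section 11.4 states: "Missing data regarding the outcome parameters and the decolonization will lead to patient dropout of the study". Section 9.2.3 gives no attrition rate and says only that "we do not expect major drop-out rates".

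**The concern.** An availability criterion is the one place where foreseeable loss of the primary outcome can be prevented before randomization. Here a single threshold serves two primary time points and matches only the shorter one. An implant patient whom the site expects to lose after, say, three months passes every criterion, although the protocol reads that patient's primary outcome at 1 year.

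The consequence depends on what happens before the patient is lost. A patient with an early infection or wound revision has a known outcome. A patient still event-free has no 1-year outcome, and section 11.4 turns that patient into a drop-out. Late implant infections in such patients are never seen.

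This differs from ordinary attrition, because the loss is anticipated at screening. An analysis plan cannot repair it afterwards: eligibility is fixed in the protocol. The target population includes patients aged 80 or over, tumor surgery and ASA scores 3-4, for whom being out of contact a year later is a realistic expectation.

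**Working it through.** **1. Time points side by side.**

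| Patient | Availability required at entry (7.1) | Primary time point (synopsis, section 5) | Minimum for remission (3.2.1) |
|---|---|---|---|
| No implant | 6 weeks | 6 weeks (day 42 +/- 14) | two months |
| Implant left in place | 6 weeks | 1 year (+/- 2 months) | 1 year |

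- Implant row: 52 - 6 = 46 weeks between the entry threshold and the primary time point. Against the early edge of the window (10 months, about 43 weeks) the gap is about 43 - 6 = 37 weeks.
- Implant-free row: two months is about 61 days. The entry threshold is 42 days, and the latest permitted Visit 3 is day 42 + 14 = 56. Both fall short of the section 3.2.1 minimum, so these three figures do not agree either.

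**2. The plan's sample size, to see what margin exists.** Inputs from sections 11.1 to 11.3: 10% against 5% events, 80% power, two-sided 0.05, 1:1 allocation.

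- Pooled-variance formula, with mean rate 0.075:
  n = [1.960 × √(2 × 0.075 × 0.925) + 0.842 × √(0.10 × 0.90 + 0.05 × 0.95)]² / 0.05² = 434.4, so 435 per arm.
- With continuity correction:
  n' = (n/4) × [1 + √(1 + 4/(n × 0.05))]² = 473.6, so 474 per arm.

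This reproduces the stated 474. Rounding up to 500 leaves 26 episodes per arm (26/500 = 5.2%), or 52 in total. The protocol does not present this margin as an allowance for loss.

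**3. How many episodes could be affected.** The protocol gives neither the implant share (p) nor the share of implant patients known at screening to be unreachable at 1 year (f). Affected episodes = 1,000 × p × f. With p assumed at 50 to 80%:

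- Each 1% of f: 1,000 × 0.50 × 0.01 = 5, up to 1,000 × 0.80 × 0.01 = 8 episodes.
- f = 3 to 10% (assumed, for anticipated short follow-up of any kind): 1,000 × 0.50 × 0.03 = 15, up to 1,000 × 0.80 × 0.10 = 80 episodes. Many such patients could still be phoned, so this range overstates the group at issue.
- f that would use up the whole margin: 5.2% / 0.50 = 10.4%, or 5.2% / 0.80 = 6.5%.

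**4. Effect on power.** All affected episodes are treated as lost, which is pessimistic because early events still count. By the uncorrected formula, power is 85.2% at 500 per arm. It is 84.7% with 15 of 1,000 lost (about 492 per arm) and 82.2% with 80 of 1,000 lost (460 per arm). Even the pessimistic end costs about 3 percentage points.

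**The case against.** **The criterion speaks of clinical follow-up, and the 1-year contact may be a phone call.** The last clinic visit required of everyone is Visit 3 at 6 weeks, so a 6-week clinical threshold is defensible on its own terms. A patient who moves away or is followed elsewhere can usually still be phoned. This stands, and it shrinks the problem to patients expected to be unreachable by any route. It does not remove the problem, because no criterion asks about reachability at 1 year.

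**The 1-year minimum in section 3.2.1 defines remission and is not an enrolment rule.** That is correct. But remission is the primary outcome term in section 5, so its definition bears on what a patient must be able to supply. The loose wording in section 5 does not rescue the 6-week threshold, because the synopsis sets 1 year for implant surgery.

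**Partial data are not missing data.** Events before loss count, and the Cox regression in section 11.3 could censor the remainder. This holds in principle. Censoring does not reveal late infections, however, and section 11.4 as written makes these patients drop-outs.

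**A longer threshold could act as a prognosis screen** and remove the high-risk patients whom the trial seeks. This is a fair warning about wording, and the fix takes it up.

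A reader might also infer two stronger points that the protocol does not support:

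- *That the primary outcome will be missing for a substantial, countable share of implant patients.* No implant share or reachability figure is given, and the phone contact may recover many of them.
- *That the comparison is biased in a known direction.* Short follow-up foreseen before randomization should be balanced between arms. Dropping only event-free patients can distort the implant event rate, but no difference between arms has been shown.

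**Conclusion.** The mismatch is real. Eligibility asks for 6 weeks of anticipated follow-up, the primary outcome for implant surgery is read at 1 year, and nothing bridges the two. An implant patient expected to be unreachable at 1 year is eligible and, if event-free when lost, leaves the analysis under section 11.4.

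The size cannot be derived from the protocol and is probably small. On an assumed implant share of 50 to 80%, it is 5 to 8 episodes per 1,000 for each 1% of implant patients unreachable even by phone. The expected harm is unseen late implant events and some loss of precision. The stated sample size does not depend on this point and reproduces as given. The correction is worth making because the loss is foreseeable and the change is one sentence, not because the effect is large.

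**What to change.** Reword the exclusion in section 7.1 and in the synopsis so that anticipated availability, by clinic visit or phone, must cover the patient's own primary time point:

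- without implant: the 6-week visit;
- with an implant: the 1-year contact, within its +/- 2 month window.

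State in the same sentence that the criterion concerns whether the patient can be contacted and is not a judgement of life expectancy or surgical risk.

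Reconcile the implant-free threshold and the 6-week visit with the two-month minimum in section 3.2.1, so that eligibility, time point and definition use the same figures.

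**Cost.** One criterion is reworded in two places and one definition is aligned. A few implant patients known to be unreachable at 1 year even by phone would not be enrolled. Counting the phone contact keeps that number low. The sample size calculation does not change.
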